#### **3.2. End-of-study KAP survey of female and male clients**

In the final three months of the study, a convenience sample of approximately 28 female clients and 28 male clients will be recruited from each of 18 sites (N=488 female and 488

male patients). All 976 participants will complete the family planning KAP survey that was used at baseline with additional questions about the acceptability of family planning services offered at the site. Note that some of these participants may have also participated in the baseline KAP survey. The final version of the survey will be submitted to the IRB prior to initiating data collection.

The survey will be administered face-to-face by an interviewer in the respondent's preferred language in a private area of the centre. Inclusion criteria for the client KAP survey will be: 1) HIV-positive woman or man obtaining care at the FACES site, 2) not currently pregnant (if female), 3) age 18 to 45 years old if female and age 18+ if male; and 4) willing and able to give informed consent. Participants will be excluded if they do not meet the inclusion criteria listed above. Participants will be reimbursed a maximum of USD\$3 (approximately 200 Kenyan Shillings at current exchange rate) for transport.

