  - a. The primary outcome upon which we based our sample size calculation is contraceptive prevalence. According to the 2003 Kenya Demographic and Health Survey, approximately 22% of women in a union in Nyanza Province use a modern contraceptive method. This level of contraceptive prevalence is similar to that seen among clients at the FACES sites. We would like to be able to detect a 8% rise in contraceptive prevalence to 30%.
- 3. Assumptions
  - a. Two-sided alpha of 0.05
  - b. Power of 0.8
  - c. Intra-cluster Correlation Coefficient of 0.01
- 4. Sample size.
  - a. Using these estimates, the needed sample size is approximately 140 women at each of the 18 sites, for a total sample of 2,520 women.
  - b. We plan to initially recruit a similar number, 2,520, of male clients, however our primary outcome for men will be the proportion of male clients who report they or their partner are interested in starting a new FP method after receiving FP counseling during their visit. In order to accurately calculate this sample size, baseline data is needed to estimate the baseline proportion of male clients who would express interest in starting a new FP method. Thus, after the baseline data collection phase a more accurate sample size for male clients will be calculated.

**KAP surveys.** Because the largest sample sizes are required for expected proportions nearer to 0.5 than to 0 or 1, we will take the worst-case scenario and assume that for each individual question on the survey approximately half of the participants will answer correctly. We hypothesize that people in the intervention sites will be more knowledgeable after the intervention at the end of the study, so we would like to test for at least a ten percentage point difference in correct answers among patients in the intervention sites (~60% correct) compared to patients in the comparison sites (~50% correct), as well as a 10% increase in correct answers among patients in the intervention sites compared to the baseline results. For a one-sided test of two proportions using two samples, power of 0.8, and an alpha level of 0.05, the required sample size is 325 patients from the intervention sites and 163 patients from the comparison sites for both men (N=488) and women (N=488).

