### **Data analysis plan**

Analyses of data from the study health facilities, given the randomized cluster design, will mainly be conducted at the cluster (health facility) level. Individual level analyses will take into account

cluster effects. Primary analyses will be based on the “intention to treat” (ITT) principle, with facilities randomized to the intervention group classified as delivering “integrated services” regardless of whether or not individual women actually received integrated services.

Preliminary analyses will be conducted to compute study outcome variables and to summarize characteristics of control and treatment sites to assess the effectiveness of randomization. Initial analyses also will involve inspection of the frequency distributions of variables to identify outlying or unusual values. Following univariate descriptions of the data, bivariate and multivariate associations will be assessed as described below.

Analysis of the primary outcomes, contraceptive prevalence and unintended pregnancy rates, and the secondary outcomes, acceptability of services and knowledge related to contraception, will be based on a comparison of means or proportions between study arms using a weighted t-test that accounts for correlations between individual outcomes within sites. Even though there are only 12 health facilities in the intervention arm and 6 health facilities in the comparison arm, each mean or percentage will be based on a relatively large number of women, and the normal approximation to the binomial distribution can be used. These tests will be evaluated based on a two-sided alternative hypothesis, 80% power, and a 5% type I error rate. The same basic approach will be used for the other primary and secondary outcomes. Results will be summarized as odds ratios for models based on binary responses (e.g. use of contraception or experiencing unintended pregnancy), and mean changes for continuous responses (e.g. score on knowledge test).

As noted above, All open-ended interviews will be tape recorded (if the woman gives informed consent), transcribed, translated to English. A content analysis will be performed using the qualitative software ATLAS.ti in order to describe themes in women’s experiences undergoing contraceptive counseling, receiving family planning methods and in the acceptability of these services.

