The baseline surveys with female and male clients will be filled out during a face-to-face interview after obtaining informed consent (see below). No identifying information will be

collected as part of the surveys, and the questionnaires will be labeled only with a study ID number that is not linked to the client's medical record.

For the open-ended interviews with clients and clinic staff, after obtaining permission from participants through an informed consent process (see below), the interviews will be audio-recorded. The recording will not be initiated until after the informed consent process is complete and any initial introductions that might include identifying information have been completed. The recording will not include the participant's name or any identifying information, only a study ID #. A separate form will be used to record information on the participant's socio-demographic characteristics (age, education, marital status, number of living children, employment, etc.) but will not include the participant's name, birth date, or specific identifying information, only the study ID #. Audio recordings will be transcribed (and translated into English if necessary) by persons who do not have access to identifying information on the participants.

**Potential Risks:** Potential risks to clients participating in the study include any social risks involved if information they reveal about their HIV status or other sensitive issues were to be disclosed outside of the research. Potential risks to clinic staff participating in the interviews include the above mentioned social risks, as well as a potential employment risk if negative information they reveal about their work environment or work practices were to be disclosed to their supervisors. Potential interview participants (both clients and clinics staff) will have the option of not participating in any part or the full interview, or refusing the audio-recording, without any adverse consequences for their medical treatment or employment.

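### Client knowledge is sized as a one-sided test of percent correct on a single question but analysed as a two-sided comparison of a test score, so the stated 80% power belongs to another quantity, and it does not hold for a single question either.

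*Protocol*

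**What the plan says.** **Sample size considerations, KAP surveys.** The planners "assume that for each individual question on the survey approximately half of the participants will answer correctly". They want to detect "at least a ten percentage point difference in correct answers among patients in the intervention sites (~60% correct") against about 50% in the comparison sites, "as well as a 10% increase in correct answers among patients in the intervention sites compared to the baseline results". The test is set out as follows: "For a one-sided test of two proportions using two samples, power of 0.8, and an alpha level of 0.05". From this, "the required sample size is 325 patients from the intervention sites and 163 patients from the comparison sites", separately for men and women (488 each). No intra-cluster correlation enters this calculation; the value of 0.01 is given only for the main trial.

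**Data analysis plan.** Knowledge is compared between arms, as means or proportions, by a weighted t-test that allows for correlation within sites, two-sided at 5% with 80% power. Binary responses are reported as odds ratios. For the other kind of response the plan reports "mean changes for continuous responses (e.g. score on knowledge test"). Analyses are mainly at facility level.

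**Endpoints.** Client knowledge is the first secondary outcome. Its data are called rates. Three contrasts are listed: pre against post within intervention sites, pre against post within control sites, and post-intervention between arms.

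**Sampling.** Each round takes a convenience sample of about 28 women and 28 men at each of the same 18 sites (sections 1.2 and 3.2). On overlap, section 3.2 says: "Note that some of these participants may have also participated in the baseline KAP survey". Under Ethical Considerations (Sources of Materials), no identifying information is collected and "the questionnaires will be labeled only with a study ID number that is not linked to the client's medical record".

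**The concern.** The sample size section treats knowledge as a set of yes/no outcomes, one per question. The analysis section treats it as one continuous score. These are different outcomes with different variances, and the sidedness of the test also differs. The 80% power in the protocol was worked out for the first and is claimed for the second.

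A later analysis plan would inherit this conflict. It could follow either section and cite the protocol, and the chance of showing a real 10-point gain would depend heavily on which one it followed. In addition, the word change has no stated meaning for clients, because the protocol describes no way to match a person's baseline and end-of-study questionnaires.

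**Working it through.** **Inputs.** From Sample size considerations: 50% and 60% correct, 163 and 325 clients, one-sided 5%, power 0.8. From the Data analysis plan: two-sided 5%, cluster-adjusted t-test. Sites: 12 and 6, so 16 degrees of freedom. Clients per site per sex: 488/18 = 27.1. Assumed, because the protocol does not give them: intra-cluster correlation (ICC) for the survey of 0.01, range 0 to 0.05; 5 to 20 questions; inter-item correlation ρ of 0.2 to 0.5.

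**1. The plan's own figure.**
- For 1:1 allocation, one-sided: n = [1.645·√(2·0.55·0.45) + 0.842·√(0.25+0.24)]² / 0.10² = 305 per arm. With continuity correction, (305/4)·[1+√(1+4/(305·0.10))]² = 325.
- So 325 is the per-arm number of a 1:1 design, and 163 is half of it, rounded up.
- For 2:1 allocation: n = (1.645+0.842)²·(0.25+0.24/2)/0.10² = 229 comparison and 458 intervention, 687 in all. With continuity correction the numbers are 243 + 486 = 729.
- The stated 325/163 is therefore not reproduced for the between-arm comparison. For the pre-post contrast within intervention sites (325 against 325) it gives 82% one-sided and 73% two-sided, ignoring clustering.

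**2. Power for one question, 10-point difference.** With item SD 0.5, SE = 0.5·√(1/163+1/325) = 0.0480, and 0.10/0.0480 = 2.08.
- One-sided: Φ(2.08−1.645) = 67%.
- Two-sided: Φ(2.08−1.96) = 55%.
- Clustered, two-sided: design effect 1+(27.1−1)·ICC, which is 1.261 at 0.01 and 2.305 at 0.05. The noncentrality falls to 2.08/√1.261 = 1.86 and 2.08/√2.305 = 1.37. Noncentral t with 16 df gives 41% and 25%.

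Using the exact variances 0.25 and 0.24 moves these by about one point.

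**3. Power for a mean percent-correct score.** For k questions, score SD = 0.5·√[(1+(k−1)ρ)/k]. It is assumed that every question shifts by 10 points. Two-sided, 16 df, ICC 0.01:

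| ρ | k = 5 | k = 10 | k = 20 |
|---|---|---|---|
| 0.2 | 83% | 91% | 94% |
| 0.3 | 75% | 82% | 85% |
| 0.5 | 61% | 65% | 67% |

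At ICC 0.05 the same table runs from 38% to 75%.

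**4. What unlinked rounds allow.** The smallest difference detectable with 80% power, two-sided, normal approximation, in score SDs for ICC 0 to 0.05:
- Post-intervention difference between arms: (1.96+0.842)·√[DE·(1/163+1/325)] = 0.27 to 0.41.
- Difference in change between arms, treating rounds as independent: the same times √2 = 0.38 to 0.58.

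Change in means can be estimated, but less precisely than the post-intervention difference.

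**The case against.** **The mismatch costs no power.** The sample size section presents the 50% assumption as a worst case, and a score usually has more power than one question. This stands in part: at ICC 0.01 the score beats the single question everywhere in the table. But it reaches 80% only under some of the assumptions, and the protocol gives neither the number of questions nor a score SD.

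**The low single-question power has other causes.** This stands. The fall from 80% to 41% comes from the halved 1:1 number, the move from one-sided to two-sided, and clustering. The mismatch in outcome does not produce it. It means that the power statement cannot be carried from one outcome to the other.

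**A mean change can be formed.** A reader might infer from the missing link between questionnaires that no change can be produced at all. The documents do not support that. The same 18 sites are surveyed in both rounds, analysis is mainly at facility level, and the endpoints already plan pre-post comparisons by arm. Only within-person change is lost. The reference to mean changes may also be loose wording for differences in means.

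**Testing many questions would inflate false positives.** A reader might infer this from the per-question sizing. With k independent questions at 5%, the chance of at least one false positive is 1−0.95^k, or 23% for 5 and 64% for 20. Nowhere does the protocol say that each question will be tested at 5%, or that one significant question would count as improved knowledge. The point therefore does not rest on this.

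**A detailed analysis plan is promised.** Score construction and item handling may properly be left to it. A contradiction between two sections of the protocol is a different matter.

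**Conclusion.** The contradiction holds. Client knowledge is sized as a one-sided per-question proportion and analysed as a two-sided, cluster-adjusted score, so the stated 80% power does not describe the planned analysis. It does not describe a single question at 325/163 either: power is about 67% one-sided and 55% two-sided before clustering. That range is arithmetic on the protocol's own inputs. The 41% (25% at ICC 0.05) rests on a survey ICC that the protocol does not state, and the 61–94% for a score also rests on an assumed number of questions, an assumed inter-item correlation and a uniform 10-point shift.

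Change for clients can mean only a difference in site or arm means. This is a secondary outcome, so the point should be corrected but does not threaten the trial's main conclusion.

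**What to change.** In Endpoints, Sample size considerations and the Data analysis plan:

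- Define client knowledge once, as each respondent's percent-correct score.
- Make the main comparison the two-sided between-arm difference in end-of-study site mean scores, adjusted for the site's baseline mean score. Both rounds are already collected and no linkage is needed.
- Replace the reference to mean changes with difference in mean score, and state that the pre-post contrasts in Endpoints are differences in site or arm means.
- Report single questions descriptively, without tests.
- Replace the per-question 80% with a power statement for the score: two-sided, 2:1 allocation, clustering included, with score SD and ICC given as assumptions over a range.

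**Cost.** No new data are needed, but this is more than rewording, because the power must be recalculated and the score SD and ICC justified. Formal claims on single questions are given up, and the stated power may be less favourable. If single-question tests were kept instead, 80% two-sided power would need about 290 + 580 = 870 clients per sex, or 366 + 732 = 1,098 at an ICC of 0.01.

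The gain from baseline adjustment is small if the ICC is near 0.01. Even with perfectly stable site effects, the correlation between a site's two means is then about 27.1·0.01/1.261 = 0.21, which removes about 0.21² ≈ 5% of the variance.

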## **TIME FRAME**

### **Study Timeline:**

|                                                                                           | Dec-
'07-
Jan '09 | Feb-
Mar '09 | Apr-
May
'09 | Jun-Jul
'09 | Aug-
Sep '09 | Oct-
Nov
'09 |
|-------------------------------------------------------------------------------------------|-------------------------|-----------------|--------------------|----------------|-----------------|--------------------|
| Conduct baseline site-based data collection                                               | X                       | X               |                    |                |                 |                    |
| Conduct baseline acceptability questionnaires and interviews with female and male clients | X                       | X               |                    |                |                 |                    |
| Finalize design of family planning integration model                                      | X                       | X               |                    |                |                 |                    |
| Conduct baseline interviews with                                                          | X                       |                 |                    |                |                 |                    |

|                                                                                            |  |   |   |   |   |   |
|--------------------------------------------------------------------------------------------|--|---|---|---|---|---|
| providers on knowledge, attitudes and practices related to family planning                 |  |   |   |   |   |   |
| Train clinicians and community health workers in integrated model                          |  | X | X |   |   |   |
| Implement the intervention at all sites                                                    |  | X | X |   |   |   |
| Post-integration data collection at all sites on pregnancy status and contraceptive use    |  |   | X | X | X | X |
| Conduct follow-up acceptability questionnaires and interviews with female and male clients |  |   |   | X | X |   |
| Interviews with providers on acceptability and feasibility                                 |  |   |   | X | X |   |
| Data analysis                                                                              |  |   |   |   |   | X |
| Dissemination of findings                                                                  |  |   |   |   |   | X |

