## **STUDY DESIGN/METHODOLOGY**

### **Overview**

The study will have three parts. During the first part (3 months), baseline data on contraceptive prevalence and unintended pregnancy will be collected at 18 PSCs that are supported by the FACES program in Suba, Kisumu East, Rongo and Migori Districts. Also during this first part, information about knowledge, attitudes and practices related to family planning will be obtained from patients and from clinicians at the sites. During the second part (3 months), an intervention consisting of integrating family planning services will be designed and implemented at twelve of the 18 FACES-supported PSCs. We aim to utilize a 2:1 integration:control model, with delayed integration so as to gradually expand the integration of FP and HIV services throughout the 18 sites, while maintaining the ability to test hypotheses on the effects of integration on health outcomes. After collecting the baseline data, we plan to stratify the clinics into two categories based on the overall patient volume and differences in the structure of family planning provision, i.e., whether or not there is a specific MCH division providing family planning at the site or not. Randomization of sites will then occur among clinics in each of these strata, with a ratio of two intervention sites (integrated model) to one control site (family planning provided in the standard manner at the site). During the third and last part (9 months), data on contraceptive prevalence and unintended pregnancy will be collected from each of the 18 sites. At the end of part three, information about knowledge, attitudes and practices related to family planning again will be obtained from female patients and from clinicians at the sites. In addition, we will administer questionnaires assessing the acceptability of family planning services to patients, and in addition clinic staff will be answer a questionnaire assessing the feasibility of providing integrated family planning services.

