## **1. Part I: Baseline data collection (Months 1-3)**

### **1.1. Baseline site-based data collection**

During a period of three months, baseline quantitative data on contraceptive prevalence, contraceptive methods used and pregnancy (including degree to which pregnancy was planned and desired) will be collected as part of routine clinical care at the 18 sites in Suba, Kisumu East, Rongo and Migori Districts. This information will be collected in a standardized clinical encounter form from all HIV-positive women age 18-45 at the time of each visit to the site. Data will also be collected on HIV-positive men age 18-45 regarding condom use, vasectomy and partner's use of other methods. A draft of the questions that will be used to collect the site-based data is included in Appendix A.

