## **2. Part II: Intervention design and implementation (Months 4-6)**

The study will be conducted as a cluster-randomized trial. Eighteen clinical sites in the Suba, Kisumu East, Rongo and Migori Districts will be randomized to a family planning intervention or to control. Sites will be grouped into strata based on the overall patient

volume and differences in the structure of family planning provision. The randomization scheme will be generated using STATA statistical software. Below we briefly outline the design and implementation of the intervention.

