### **3. Part III: Post-intervention data collection (Months 7-15)**

#### **3.1. Post-intervention site-based data collection**

Over the following nine months, data on contraceptive prevalence, contraceptive methods used and pregnancy (including degree to which pregnancy was planned and desired) will be collected, as part of routine care, at the 18 sites (twelve intervention and six control sites) among women age 18-45 and men age 18 and older. Data will also be collected on whether contraceptive counseling was performed at each clinic visit. This information will be collected in the standardized clinic encounter form from all HIV-positive women and men at the time of each visit to the site. At each of the sites, a random sample of 10-15% of all charts will be reviewed during the post-intervention period to determine if the family planning module of the clinical encounter form is being filled out. A draft of the questions that will be used to collect the site-based data is included in Appendix A.

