### **KEMRI**

#### Personnel (all staff receive benefits at 15%)

- [name] will serve as Site PI and will be supported at 1% effort. [name] will give additional in-kind support of approximately 9%.
- A nurse/researcher will serve as the Family Planning coordinator to coordinate the project and will be supported full-time.
- An assistant coordinator also trained as a nurse will also be supported full-time.
- Four nurses who specialize in family planning will be supported full-time to mentor and assist clinicians with FP integration at the 18 sites.
- Three interviewers will be hired to conduct interviews with clients and clinicians.
- Three data clerks will be supported full-time to perform data entry for the electronic medical records (OpenMRS system) and manage the data. An additional \$3,000 is requested to support approximately 80% of an additional data clerk to perform data entry for the surveys and questionnaires detailed in the proposal.
- [name], the FACES Program Manager based at KEMRI, will be supported at 10% to perform administrative duties and supervise financial management.
- [name], a statistician based at KEMRI, will be supported at 5% to assist with data analysis.
- Health insurance costs of \$3,934 are requested to provide the twelve 100% EFT employees with health insurance. The current health insurance premium is 20,000 Ksh per annum per 100% EFT employee; this translates into \$327.87 US dollars.

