#### Travel

\$9,000 is requested to support local travel throughout Nyanza Province over the course of the year-long project. To the extent possible, travel related to the project will be coordinated with other FACES activities to take advantage of program vehicles.

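### The study timeline contradicts the design text on which sites get the intervention, when outcome collection starts, and how long it lasts

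*Protocol*

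**What the plan says.** **Design text.** The Overview under Study Design/Methodology describes three consecutive parts. In the second part, "an intervention consisting of integrating family planning services will be designed and implemented at twelve of the 18 FACES-supported PSCs". The section headings fix the order: "Part I: Baseline data collection (Months 1-3"), then "Part II: Intervention design and implementation (Months 4-6"), then "Post-intervention data collection (Months 7-15"). Section 3.1 has twelve intervention and six control sites during Part III. The Overview and section 2.2 also foresee that all 18 sites will eventually be integrated, without a date for the six controls.

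**Endpoints.** Both primary outcomes compare the arms on post-intervention data from the same period. The pregnancy rate is the number of pregnancies divided by the unique clients seen in the post-intervention collection period.

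**Study Timeline.** One row reads "Implement the intervention at all sites" and is marked in Feb-Mar and Apr-May 2009, as is the training row. Another reads "Post-integration data collection at all sites on pregnancy status and contraceptive use" and is marked from Apr-May to Oct-Nov 2009.

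**Budget justification.** The KEMRI travel item speaks of local travel "over the course of the year-long project". The KEMRI personnel item funds nurses to "mentor and assist clinicians with FP integration at the 18 sites".

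**The concern.** The chart is the only place where the design is put on calendar dates, so site staff and data clerks are likely to work from it. It departs from the design in three ways: the sites that receive the intervention, whether outcome collection waits for implementation to finish, and the length of the outcome window.

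The second and third bear on both primary outcomes. Records from an intervention site that is not yet integrated reflect usual referral care, yet under intention to treat they count in the intervention arm and pull the difference towards zero. The pregnancy rate is the more exposed. It accumulates events over the whole window, and a pregnancy recorded in April or May 2009 could have been conceived before the site was integrated. Contraceptive prevalence may be less affected, depending on how it is derived from repeat visits.

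The site wording matters because the trial has only six control sites, and each one integrated before the last outcome record would lose its value as a comparator.

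**Working it through.** **1. Calendar against design**

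| Item | Design text | Study Timeline |
|---|---|---|
| Sites receiving the intervention | 12 of 18 | all sites |
| Implementation | Months 4-6 | Feb-May 2009 |
| Outcome collection | Months 7-15, after Part II | Apr-Nov 2009 |
| Length of outcome collection | 15 - 7 + 1 = 9 months | 4 columns x 2 months = 8 months |
| Overlap with implementation | none | Apr-May 2009, up to 2 months |

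The overlap is at most 2/8 = 25% of the charted outcome period. The columns are two months wide, so the two activities could run one after the other inside April-May. That removes the overlap but shortens the window: collection from May gives 7 months and from June gives 6. No reading of the chart gives nine months, and this does not depend on when the chart begins.

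**2. The plan's own power, reproduced first**

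Inputs from Sample size considerations: 22% against 30%, two-sided alpha 0.05, power 0.80, intra-cluster correlation 0.01, 140 women per site, 12 and 6 sites.

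- Design effect = 1 + (140 - 1) x 0.01 = 2.39.
- Effective numbers: control 6 x 140 / 2.39 = 351.5; intervention 12 x 140 / 2.39 = 702.9.
- Standard error = sqrt(0.22 x 0.78/351.5 + 0.30 x 0.70/702.9) = 0.0281.
- Ratio of effect to standard error = 0.08/0.0281 = 2.85.
- Power: 79% (normal, pooled variance under the null), 81% (normal, unpooled), 76% (noncentral t with 18 - 2 = 16 df).

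The stated 80% is reproduced by the normal approximation that the Data analysis plan names.

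**3. Dilution, as an illustration**

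Let u be the share of the two overlap months that is un-integrated at intervention sites. If visits are spread evenly over eight months and all are pooled, the observed effect is 8 x (1 - (2/8) x u) points. The documents give no value for u, so the range is shown. The standard error is recalculated at each diluted prevalence.

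| u | Effect | Prevalence, intervention | t, 16 df | Normal, pooled | Normal, unpooled |
|---|---|---|---|---|---|
| 0 | 8 points | 30% | 76% | 79% | 81% |
| 0.5 | 7 points | 29% | 65% | 68% | 71% |
| 1 | 6 points | 28% | 53% | 56% | 58% |

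At 200 women per site, the protocol's conservative estimate of eligible women, the design effect is 1 + 199 x 0.01 = 2.99. A 7-point effect then has 71% power (t, 16 df) or 76% (normal, unpooled).

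**4. Control sites**

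For keeping them as controls: the Overview (delayed integration that preserves the hypothesis test), section 2.2 (control care defined), section 3.1 (six control sites in Part III), Endpoints (same-period comparison), and Expected Application of Results (wider introduction depends on the trial's findings). Reading otherwise: the timeline row and the nurse item in the budget. No section gives a date before which control sites may not be integrated.

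**The case against.** The strongest reply is that this is a clerical mismatch, and that one loosely worded row does not override the operative sections. Much of that stands.

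- **Control arm.** A reader might infer from the timeline that the control arm is unprotected. The documents do not support that. Five sections, listed above, keep six controls or tie roll-out to the results. The row may be shorthand for all intervention sites. Section 2.2 also puts the family planning module on encounter forms in both arms, which could explain the wording. The budget text is weak evidence, since it is out of step elsewhere: it pays for 640 client interviews, while the design plans 976 KAP surveys per round. What stands is the conflicting wording and the missing date.
- **Baseline.** Baseline collection and implementation are both marked in Feb-Mar 2009, so a reader might infer that late baseline data follow allocation. With a December 2008 start, a three-month baseline (Dec-Feb) and a three-month implementation (Mar-May) would both mark that column. The Overview already places randomisation after baseline, and the primary comparison is between arms after the intervention.
- **Fifteen months in twelve.** A reader might infer that a 15-month design has been squeezed into a funded year. That requires reading the printed Dec '07 in the first column as Dec '08. That is plausible, but it is not what is printed. The budget table covers an initial period, which leaves room for later funding, although the travel item points the other way.
- **Dilution.** The overlap may be nil, and starting collection does not by itself fix the analysis window. If prevalence were taken from each woman's last visit, dilution would be small or absent.

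The last-visit answer does not help the pregnancy rate, which counts events over the window. Removing the overlap also moves the window further from nine months.

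**Conclusion.** The point holds in a limited form. As printed, the timeline contradicts the design text in three respects: all sites against twelve, outcome collection marked alongside implementation for up to two of eight months, and at most eight post-intervention months against nine. None of these depends on an assumption about the chart's first column.

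The consequence is conditional. If the chart is followed, outcome records will include some time before integration is complete, and the contrast between arms is diluted by an unknown amount. The power losses above illustrate that effect for prevalence. They assume 140 women per site, pooled and evenly spread visits, and half to all of two months un-integrated. They are not a forecast. The normal approximation and the 16-df reference start from different levels but show a similar loss.

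On the control sites, the supportable statement is that two places conflict with the design and that no hold date is given. The opening date and length of the window help define a primary endpoint, so the contradiction should be corrected, and text changes are enough.

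**What to change.** Reconcile the Study Timeline with Parts I-III:

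1. Reword the implementation row to name the 12 intervention sites, and align the nurse item in the budget justification.
2. Open the post-intervention analysis window on one calendar date for both arms, after implementation is complete at the intervention sites. Encounter-form data may still be recorded earlier as routine care.
3. State that control sites are not integrated before the last post-intervention record.
4. State the window that the calendar delivers, about six months (June-November 2009) if implementation runs through May 2009, or move the end date to give nine.
5. Correct or confirm the date in the first column.

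**Cost.** A protocol and timeline amendment. The stated follow-up may become shorter than nine months, which leaves less time to observe pregnancies. Keeping nine months means a later end date and may need funding beyond the initial budget period.
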